### Genotyping

Genomic DNA was isolated from EDTA blood samples with the QIAamp DNA Blood Kit (Qiagen). Saliva was collected with the Oragene DNA collection kit (DNA Genotec), and genomic DNA was extracted from saliva samples using the prepIT L2P reagent (DNA Genotec). DNA was quantified by Quant-iT PicoGreen assay (Invitrogen), according to the manufacturer’s protocols. Genomic DNA samples were genotyped for *RARG* rs2229774, *SLC28A3* rs7853758, and *UGT1A6* rs17863783 (Table 2) by TaqManSNP genotyping (Applied Biosystems), using the Type-it Fast SNP Probe PCR Kit (Qiagen) with predesigned primers and probes (Applied Biosystems).

Laboratory assistants were blinded to the case-control status of the patients genotyped in the study. To ensure the accuracy of all genotyping results, multiple positive and negative controls and replicate samples were included in all genotyping assays and plates. The concordance of genotype calls between replicate genotyped samples was 100%.

Genomic DNA will also be used to replicate the association of doxorubicin-related cardiovascular toxicity with other candidate genes that have been described [22] or that will be discovered in the future, provided our sample size is sufficient.

**Table 2 table2:** Overview of the single nucleotide polymorphisms tested in LESS-Anthra.

Gene	Reference SNP^a^ cluster ID	Alleles (Ref^b^>Alt^c^)	Chromosome	MAF^d^ (1000 Genomes, European population)	Gene consequence	Amino acid/codon change
*RARG*	rs2229774	G>A	12	A=0.064	Missense variant	NP_000957.1: p.Ser427Leu
*SLC28A3*	rs7853758	G>A	9	A=0.137	Synonymous variant	Leu (CTG)>Leu [TTG]
*UGT1A6*	rs17863783	G>T	2	T=0.023	Synonymous variant	Val (GTG)>Val [GTT]

^a^SNP: single nucleotide polymorphism.

^b^Ref: reference allele.

^c^Alt: alternative allele.

^d^MAF: minor allele frequency.

### Estimation of Case Numbers for the Pharmacogenetic Studies

The appropriate case number was estimated based on a published study of the association of the nonsynonymous *RARG* gene variant p.Ser427Leu (rs2229774) with anthracycline-induced cardiomyopathy (combined analysis of the discovery and replication cohorts: odds ratio 4.7, 95% CI 2.7-8.3; *P*<.001) [12]. Assuming an odds ratio of 4.7, an allele frequency (controls) of 6.4%, an alpha error of 5%, power of 80%, a control: case ratio of 3:1, and a dropout rate of approximately 10%, at least 33 cases and 99 controls, will be required to replicate with sufficient statistical power the association of *RARG* rs2229774 with anthracycline-induced cardiomyopathy.

### Data Collection

For data collection, the electronic ObTiMA system ontology-based trial management application was used [23]. ObTiMA has been validated for clinical trials. Every correction made to the entered data is traceable. Only authorized persons have access to the program and the data. Data backups occur regularly and automatically. In ObTiMA, electronic case report forms for capturing all patient data have been defined for this study. All data were pseudonymized before entry into the database of ObTiMA and handled according to the European General Data Protection Regulation.

### Statistical Analysis

The *RARG* rs2229774, *SLC28A3* rs7853758, and *UGT1A6* rs17863783 SNPs were checked for deviations from Hardy-Weinberg equilibrium (HWE). Departure from HWE was defined as *P*-HWE <.01 (after Bonferroni correction of the nominal value of *P* set at .05) and tested by a χ^2^ test of goodness of fit between the observed and expected genotypes.

Our primary aim was to assess the value of multimarker genetic testing for *RARG* rs2229774, *UGT1A6* rs17863783, and *SLC28A3* rs7853758 for predicting doxorubicin-induced cardiovascular dysfunction. To address that aim, we considered the following 3 predictive models. Model 1 includes only clinical risk factors, such as sex, age, irradiation (mediastinal, lung, or left abdominal), the use of other cardiotoxic drugs, length of follow-up, and cumulative dose of doxorubicin. Model 2 includes only genetic profiling. For each individual, the genetic risk will be scored as suggested by the Canadian Pharmacogenomics Network for Drug Safety (CPNDS) Clinical Practice Recommendations Group [14], based on multimarker genetic testing for *RARG* rs2229774, *UGT1A6* rs17863783, and *SLC28A3* rs7853758. Patients carrying the *RARG* rs2229774 A or *UGT1A6* rs17863783 T risk variants will be classified as high genetic risk; patients carrying the *SLC28A3* rs7853758 A protective variant who do not carry *RARG* rs2229774 A or *UGT1A6* rs17863783 T alleles will be classified as low genetic risk; all other patients will be classified as moderate genetic risk (Table 3). Model 3 includes both clinical risk factors and genetic profiling. The independent contribution of each risk factor to the outcomes will be determined using multivariable logistic regression analysis. The predictive accuracy of the model will be assessed by the area under the receiver operating characteristic curve.

**Table 3 table3:** Genetic risk scoring of anthracycline-associated cardiotoxicity as suggested by the Canadian Pharmacogenomics Network for Drug Safety Clinical Practice Recommendations Group [14].

Genetic risk^a^	RARG^b^ rs2229774	UGT1A6^c^ rs17863783	SLC28A3^d^ rs7853758
High	A|G or A|A	Any genotype	Any genotype
High	Any genotype	G|T or T|T	Any genotype
Moderate	G|G	G|G	G|G
Low	G|G	G|G	A|A or A|G

^a^Risk scoring depends on the combined evaluation of three genetic markers, the polymorphisms rs2229774 in *RARG*, rs17863783 in *UGT1A6*, and rs7853758 in *SCL28A3*.

^b^RARG: retinoic acid receptor gamma.

^c^UGT1A6: UDP glucuronosyltransferase family 1 member A6.

^d^SLC28A3: solute carrier family 28 member 3.

Our secondary aim is to replicate the previously described associations of candidate genetic markers with anthracycline-induced cardiotoxicity if our sample size has sufficient statistical power. Association of the candidate SNPs with the outcome will be performed using logistic regression, adjusting for sex; age; mediastinal, left abdominal, and lung irradiation; the use of other cardiotoxic drugs; length of follow-up; and cumulative dose of doxorubicin. The Benjamini-Hochberg False Discovery Rate will be used to account for multiple testing.

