**Objective:**

The primary aim of this study is to evaluate the value of multimarker genetic testing for RARG rs2229774, UGT1A6 rs17863783, and SLC28A3 rs7853758 for predicting doxorubicin-induced cardiotoxicity. The secondary aim is to replicate previously described associations of candidate genetic markers with doxorubicin-induced cardiotoxicity. Moreover, we will evaluate the prevalence of cardiovascular dysfunction in childhood cancer survivors after neuroblastoma or nephroblastoma.

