The primary aim of this study is to evaluate the importance of multimarker genetic testing for *RARG* rs2229774, *UGT1A6* rs17863783, and *SLC28A3* rs7853758 for predicting doxorubicin-induced cardiovascular dysfunction. We focus on these 3 markers because the only pharmacogenetic guideline published to date recommends their testing to stratify the individual cardiotoxic risk of anthracycline therapy. The secondary aim of this study is to determine the association of doxorubicin-induced cardiovascular toxicity with other candidate genes that have been previously described [13,16-19] or will soon be discovered, provided that our sample size has sufficient statistical power. To ensure that the population studied is as homogeneous as possible in terms of diagnoses and the type of anthracycline used, we focus on patients with childhood nephroblastoma or neuroblastoma. Another secondary objective is to investigate the prevalence of cardiovascular dysfunction in a population of children treated with doxorubicin.

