### Outcomes

The primary endpoint was cardiac dysfunction, as diagnosed by the cardiologist or revealed by a central assessment of transthoracic echocardiography. Cardiac dysfunction is presumed when at least one of the following criteria is true:

Diagnosis by the cardiologist of heart failure or cardiomyopathy reported in the questionnaire.Left ventricular ejection fraction reduced to <50%.Shortening fraction reduced to <25%.Relative wall thickness reduced to <0.22.Percentage systolic thickening of the interventricular septum and left ventricular (LV) posterior wall reduced to <33%.LV Tei index (myocardial performance index) >0.40.Right atrial volume at end systole/body surface area >30 ml/m^2^.

The secondary endpoint is cardiovascular dysfunction, defined as the composite of arterial hypertension (diagnosed by the cardiologist and reported in the questionnaire or current blood pressure measured during the visit ≥140 mmHg systolic or ≥90 mmHg diastolic), cardiac arrhythmia (diagnosed by the cardiologist and reported in the questionnaire), and cardiac dysfunction (as defined above).

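### The primary aim is worded on cardiovascular dysfunction, which the Outcomes section defines as the secondary endpoint, so it is unclear which outcome carries the primary comparison of Models 1-3

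*Protocol article*

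**What the plan says.** Outcomes defines two binary endpoints and ranks them. First: "The primary endpoint was cardiac dysfunction, as diagnosed by the cardiologist or revealed by a central assessment of transthoracic echocardiography". Then: "The secondary endpoint is cardiovascular dysfunction, defined as the composite of arterial hypertension", together with arrhythmia and cardiac dysfunction itself. The second endpoint therefore contains the first.

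The primary aim is worded in three places:

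- Abstract, Objective: "rs7853758 for predicting doxorubicin-induced cardiotoxicity". Cardiotoxicity is not one of the two defined endpoints.
- Introduction, last paragraph: "for predicting doxorubicin-induced cardiovascular dysfunction. We focus on these 3 markers".
- Statistical Analysis: "for predicting doxorubicin-induced cardiovascular dysfunction. To address that aim, we considered the following 3 predictive models". These are the clinical model, the genetic model and the combined model.

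The sentence on fitting names no endpoint: "The independent contribution of each risk factor to the outcomes will be determined using multivariable logistic regression analysis". The sentence on the AUC names none either.

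**The concern.** The aim that Models 1-3 serve and the endpoint ranked first carry different names, and the name used in the aim is the defined name of the other endpoint. An analyst who applies the article's own definitions to its stated aim would run the main comparison on a composite that counts hypertension and arrhythmia. An analyst who starts from Outcomes would run it on cardiac dysfunction. Both could claim to have followed the plan.

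Two things are at stake:

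- **Selection.** The article already tabulates genotypes and risk groups (Results, Genotyping), the database is not yet closed (Results, Data Collection), and the Discussion says outcome definitions may still be adjusted. If two outcomes can both claim primary status, the more favourable AUC or odds ratio could be reported as the main one. The false discovery rate procedure is stated under the secondary candidate-SNP aim and does not cover this choice.
- **Meaning.** The risk score was proposed for anthracycline cardiotoxicity. If the added hypertension and arrhythmia are unrelated to genotype, they dilute the contrast between risk groups.

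**Working it through.** **1. The wordings side by side**

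| Place in the article | Role | Outcome named |
|---|---|---|
| Outcomes | primary endpoint | cardiac dysfunction |
| Outcomes | secondary endpoint | cardiovascular dysfunction |
| Abstract, Objective | primary aim | cardiotoxicity |
| Introduction | primary aim | cardiovascular dysfunction |
| Statistical Analysis | primary aim, Models 1-3 | cardiovascular dysfunction |
| Statistical Analysis | regression | outcomes, plural |
| Estimation of Case Numbers | planning outcome | cardiomyopathy |

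The mismatch occurs twice in the wording of the primary aim, and nothing in the article reconciles it.

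**2. The plan's own figure**

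The stated 33 cases and 99 controls reproduce, so the sample-size arithmetic is not at fault. Inputs from Estimation of Case Numbers: odds ratio 4.7, control allele frequency 0.064, alpha 5%, power 80%, k = 3 controls per case, dropout about 10%. Sidedness is not stated; a two-sided test is assumed.

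- Carrier frequency in controls, assuming Hardy-Weinberg equilibrium: p0 = 1 - (1 - 0.064)² = 0.1239.
- Carrier frequency in cases: odds 4.7 × 0.1239/0.8761 = 0.6647, so p1 = 0.6647/1.6647 = 0.3993. Difference d = 0.2754; pooled pb = (0.3993 + 3 × 0.1239)/4 = 0.1928.
- n = [1.96·√(pb(1-pb)(1+1/k)) + 0.8416·√(p1(1-p1) + p0(1-p0)/k)]² / d² = 23.5.
- With continuity correction: (n/4)·[1 + √(1 + 2(1+1/k)/(n·d))]² = 28.1, rounded up to 29.
- Dropout: 29/0.9 = 32.2, rounded up to 33 cases; 3 × 33 = 99 controls.

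This calculation concerns cardiomyopathy. Naming cardiac dysfunction as the primary outcome leaves it unchanged.

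**3. How much the choice could matter (illustration only)**

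From Table 7: 72 high-risk patients and 301 + 107 = 408 others, so the high-risk share is 72/480 = 0.15. Assumed, not in the article: prevalence P of cardiac dysfunction, the high-risk odds ratio, and a share e with hypertension or arrhythmia that is independent of genotype and of cardiac dysfunction.

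- Solve 0.15·p1 + 0.85·p0 = P with p1/(1-p1) = OR·p0/(1-p0).
- Composite risk in each group: p' = p + (1-p)·e.
- Two-sided 5% power = Φ((d - 1.96·s0)/s1), with s0 = √(pb(1-pb)(1/72 + 1/408)), s1 = √(p1(1-p1)/72 + p0(1-p0)/408), and pb now the overall risk.

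Worked case, P = 0.10 and OR 3:

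- p0 = 0.0808, p1 = 0.2087, d = 0.1279, s0 = 0.0383, s1 = 0.0498.
- Power = Φ(1.06) = 0.86.
- With e = 0.10 the risks become 0.1727 and 0.2878. The odds ratio is (0.2878/0.7122)/(0.1727/0.8273) = 1.94 and power is 0.62.

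| Assumed OR | P | Power, cardiac dysfunction | Composite, e = 10%: OR, power | Composite, e = 30%: OR, power |
|---|---|---|---|---|
| 3 | 10% | 0.86 | 1.94, 0.62 | 1.45, 0.31 |
| 3 | 15% | 0.93 | 2.17, 0.80 | 1.64, 0.49 |
| 3 | 30% | 0.99 | 2.56, 0.96 | 2.08, 0.80 |
| 4.7 | 10% | 0.99 | 2.60, 0.90 | 1.75, 0.59 |
| 4.7 | 15% | >0.99 | 3.06, 0.98 | 2.09, 0.82 |

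**The case against.** The strongest reply is that this is loose terminology. Outcomes does name one primary endpoint. The article also moves freely between cardiotoxicity, cardiovascular toxicity and cardiovascular dysfunction. The abstract keeps cardiovascular dysfunction for the prevalence aim, and the case number rests on cardiomyopathy; both sit closer to the declared primary endpoint. The term in Statistical Analysis stands in a restatement of the aim, and the plural in the regression sentence fits models run on both endpoints with the ranking set in Outcomes. The full protocol or SAP may also name the model outcome.

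Much of this stands, and it rules out two stronger readings. A reader might infer that the study has no single primary outcome. It has one; what differs is the outcome in the wording of the primary aim. A reader might also infer that the main models will be fitted to the composite. That is the literal reading of the aim, but no sentence specifies it for the models.

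It does not remove the point. The term in the aim is the exact one that Outcomes reserves for the secondary endpoint, and it appears in two sections. Nor is this a detail properly left to the SAP: two stated passages conflict, and an SAP could follow either.

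The reply also limits the power figures. None of the prevalences, the odds ratio of 3, the added 10-30% or the independence from genotype comes from the article. Any one of seven criteria counts as cardiac dysfunction, so prevalence may exceed 15%; the Introduction cites 4.4%-42% for cardiac abnormalities in earlier survivor studies. The article's only planning odds ratio, 4.7, is for RARG alone. The illustration also compares two groups, whereas the plan uses three risk groups and judges prediction by AUC.

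**Conclusion.** The point holds as an unresolved contradiction. The primary endpoint is cardiac dysfunction, but the primary aim behind Models 1-3 is worded on the secondary endpoint, so the outcome for the main comparison and its AUC is ambiguous. This rests on the text alone.

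The size of the consequence is not established. If the added events are unrelated to genotype, the direction is dilution. The power loss ranges from slight (0.99 to 0.96) to severe (0.86 to 0.31) over the odds-ratio-3 scenarios, all of them assumed. A reader might go further and argue that hypertension in these survivors has other causes; the article offers nothing to support that, and the point does not need it.

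**What to change.** Before database closure, reconcile the abstract's Objective, the last paragraph of the Introduction, Outcomes and Statistical Analysis by naming one outcome for the primary comparison of Models 1-3 and its AUC. Cardiac dysfunction as defined in Outcomes is the natural choice: it is already declared primary and is closest to the cardiomyopathy outcome behind the case number. State that the same models on cardiovascular dysfunction are secondary, and replace the unspecified plural in the regression sentence with the named endpoints.

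The cost is a change of wording. It needs no new data and leaves the 33/99 calculation as it is. It protects the result only if it is dated before outcomes are analysed by genotype.

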## Introduction

Despite the emergence of new so-called targeted therapies, standard cytotoxic chemotherapies remain a cornerstone for treating various cancers. Anthracyclines, such as doxorubicin, daunorubicin, and epirubicin, are still among the most used chemotherapeutic agents. However, cardiotoxicity is a frequent complication with this class of anticancer drugs. In particular, childhood cancer survivors are at risk for cardiovascular complications, with a 15-fold increase in the relative risk of severe congestive heart failure compared to their noncancer siblings [1] and an 8-fold increase in mortality due to cardiovascular disease compared to the overall population [2,3]. Previous studies showed that 4.4%-42% of childhood survivors of acute lymphoblastic leukemia or nephroblastoma had progressive cardiac abnormalities several years after completing doxorubicin therapy [4-6].

Anthracycline-induced cardiomyopathy may develop during treatment or several years after completion of treatment and may include decreased left ventricular ejection fraction and signs and symptoms of congestive heart failure. Many risk factors for anthracycline-induced cardiotoxicity have been identified, most notably higher cumulative anthracycline doses and younger age. However, the optimal strategy for the prevention of anthracycline-induced cardiotoxicity is unclear. Currently, dexrazoxane is the only treatment for anthracycline cardioprotection approved by the United States Food and Drug Administration and European Medicines Agency. However, dexrazoxane is contraindicated in children and adolescents due to a 3-fold higher incidence of secondary malignancies in dexrazoxane-treated children compared with controls.

There is an additive or potentially synergistic increase in the risk of cardiomyopathy or cardiovascular death in anthracycline-treated patients who have received radiotherapy to the mediastinum or concomitant therapy with other known cardiotoxic agents, such as cyclophosphamide or vinca alkaloids [7,8]. Tukenova et al [7] reported that as little as 5 Gy of radiation to the heart increased the relative risk of cardiovascular disease mortality in childhood cancer survivors. New techniques in radiotherapy can increase cardiac protection without losing the efficacy of irradiation [9].

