## Results

### Recruitment

This cohort study evaluates the risk of developing anthracycline-induced cardiotoxicity in survivors (ie, survival for 5 years or more after diagnosis) of pediatric nephroblastoma or neuroblastoma. A review of the German Childhood Cancer Registry database revealed 2158 eligible patients (943 nephroblastoma and 1215 neuroblastoma patients) who were invited by mail to participate in the study (Figure 1).

Patient recruitment started in June 2017 and was completed in September 2018. There were 657 patients (284 neuroblastoma and 373 nephroblastoma patients) who consented to participate in the LESS-Anthra study, and 480 (73%) of these patients provided a biospecimen for pharmacogenetic studies. Table 4 summarizes the baseline characteristics of participants and nonparticipants of LESS-Anthra.

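### The primary aim rests on the AUCs of nested models in one cohort, with no optimism correction and no named comparison of Model 3 with Model 1

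*Protocol article*

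**What the plan says.** The Statistical Analysis section of the protocol article sets out three models for the primary aim. The first is clinical: "Model 1 includes only clinical risk factors, such as sex, age, irradiation (mediastinal, lung, or left abdominal), the use of other cardiotoxic drugs", followed by length of follow-up and cumulative doxorubicin dose. The second uses only the genetic score, in three classes fixed beforehand from an outside guideline (Table 3). For the third, "Model 3 includes both clinical risk factors and genetic profiling".

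Two sentences of method follow. One covers the individual terms: "The independent contribution of each risk factor to the outcomes will be determined using multivariable logistic regression analysis". The other covers prediction: "The predictive accuracy of the model will be assessed by the area under the receiver operating characteristic curve".

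The Recruitment section describes one genotyped sample: "480 (73%) of these patients provided a biospecimen for pharmacogenetic studies". The article mentions no second cohort, hold-out sample or resampling. It does not say whether the score enters as categories or as an ordered number, and it gives no rule for comparing Model 3 with Model 1.

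**The concern.** Model 3 is Model 1 plus the score. When both are fitted and scored in the same patients, the extra terms adapt to chance patterns, and the AUC tends to rise even if the genes carry no information. Each AUC is also too high in itself as a forecast of performance in new patients.

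The article presents the study as the first evaluation of the combined test's ability to predict cardiotoxicity (Discussion). Readers will look to the AUCs of Models 1 and 3 for that answer. Without a stated comparison or correction, a small rise could be taken as evidence for the test, and the AUCs as an estimate of its accuracy in practice.

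**Working it through.** **1. The plan's own design figure.** Inputs (Estimation of Case Numbers): odds ratio 4.7, control allele frequency 6.4%, alpha 5%, power 80%, three controls per case, about 10% dropout.
- Control carrier rate: 1 − (1 − 0.064)² = 0.124.
- Case carrier rate: odds 0.124/0.876 × 4.7 = 0.665, so 0.665/1.665 = 0.399.
- Two-proportion formula, two-sided, with continuity correction: 29 cases. 29/0.90 = 32.2, so 33 cases and 3 × 33 = 99 controls.

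This matches the article. The carrier model, two-sidedness and continuity correction are my assumptions; other variants give 17 to 49 cases. The figure concerns one RARG association and does not address a gain in AUC.

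**2. Sign and size of the AUC gain when genes add nothing.** Inputs from the article: n = 480; score classes 72/301/107 (Table 7); six clinical predictors. The article does not give the outcome prevalence in this cohort. I used the range it cites for earlier studies, "4.4%-42% of childhood survivors of acute lymphoblastic leukemia or nephroblastoma had progressive cardiac abnormalities", which is 0.044 × 480 = 21 to 0.42 × 480 = 202 cases. The predictor distributions and the strength of the clinical signal are assumptions. Both models were fitted and scored on the same patients, with 800 to 1,500 runs per setting and d = AUC(Model 3) − AUC(Model 1). A selection:

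| Prevalence | Clinical signal | Score coding | Share with d > 0 | Mean d |
|---|---|---|---|---|
| 4.4% | moderate | 3 categories | 0.879 | 0.0186 |
| 4.4% | moderate | ordinal | 0.753 | 0.0089 |
| 4.4% | strong | 3 categories | 0.835 | 0.0107 |
| 4.4% | strong | ordinal | 0.712 | 0.0051 |
| 25% | none | 3 categories | 0.907 | 0.0119 |
| 25% | none | ordinal | 0.804 | 0.0066 |
| 25% | moderate | 3 categories | 0.870 | 0.0055 |
| 25% | moderate | ordinal | 0.776 | 0.0031 |
| 42% | strong | 3 categories | 0.889 | 0.0025 |
| 42% | strong | ordinal | 0.759 | 0.0013 |

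Over all settings the share is 84% to 92% with categories and 71% to 80% with ordinal coding. With categories and a moderate clinical signal, d exceeds 0.02 in 27% of null runs at 7% prevalence and in 3% at 25%.

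**3. Inflation of each AUC.** Separate null runs with 33, 48 and 96 cases (7%, 10% and 20% of 480), a three-category score, and the fitted models scored again in 60,000 new patients:

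| Cases | Model 1: fitted − new | Model 3: fitted − new | Gain in fitted sample |
|---|---|---|---|
| 33 | 0.679 − 0.603 = 0.076 | 0.692 − 0.595 = 0.097 | 0.692 − 0.679 = 0.013 |
| 48 | 0.670 − 0.612 = 0.058 | 0.680 − 0.605 = 0.075 | 0.680 − 0.670 = 0.010 |
| 96 | 0.656 − 0.621 = 0.035 | 0.663 − 0.615 = 0.048 | 0.663 − 0.656 = 0.007 |

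Repeat runs with other assumed covariates put Model 3's inflation at about 0.11 for 7% prevalence and 0.034 to 0.04 for 42%.

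**4. With the remedy.** In null data with a moderate clinical signal and prevalence of 7%, 15% and 25% (200 runs, 40 resamples each), the bootstrap-corrected difference averages −0.003 to +0.001. It is positive in 25% to 40% of runs. The likelihood-ratio test of the genetic terms rejects in 5% to 7% of null runs in the 1,500-run settings; the highest values (6.2% and 7.1%) come with about 21 cases and the categorical score.

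**The case against.** The strongest reply is that the document does not say what this concern presumes. A reader might infer that the plan commits to uncorrected AUCs in the fitting sample and will declare the test useful if Model 3's AUC is higher, so that a favourable result is nearly certain. The text supports neither step. It does not say the AUCs are uncorrected, it sets no rule that a higher AUC means value, and a condensed article may leave resampling to a fuller plan. Nor does it mention a significance test of the AUC difference, so no criticism can rest on the behaviour of such a test.

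Three further points stand:
- The multivariable regression assesses the genetic terms adjusted for the clinical factors, and a joint test of those terms holds close to its 5% level.
- The score classes come from outside the data, so only one or two genetic coefficients are estimated and the spurious gain is small.
- Most of the inflation is shared by Model 1 (0.076 of 0.097 with 33 cases) and cancels in the comparison.

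The reply does not remove the point. The article does specify the analysis of its primary aim, and the one accuracy measure it names comes with neither a comparison nor a safeguard. The regression sentence speaks of each factor's contribution; it does not name a joint test of the score or say that this test decides added value. The regression also does nothing about the inflation of the AUCs themselves.

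**Conclusion.** The point holds as a cheap improvement, not as a must-fix error. If the AUCs are taken in the fitting sample, they overstate performance in new patients by roughly 0.03 to 0.11, with the larger figures when cases are few. Ranking Models 1 and 3 by those AUCs would favour Model 3 in about 84% to 92% of studies with uninformative genes under three-category coding, or 71% to 80% under ordinal coding, usually by 0.015 or less.

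These figures rest on same-sample scoring, which is inferred from there being a single cohort; on an assumed prevalence (7% to 42% for the inflation, 4.4% to 42% for the ranking); and on assumed covariate distributions and clinical signal. A figure of nine in ten is therefore tied to the categorical score and describes the sign of the gain, not a material improvement.

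**What to change.** Add to the Statistical Analysis section:
- how the genetic score is coded;
- that added value is tested by the likelihood-ratio test of Model 3 against Model 1 (2 df if the score is categorical, 1 df if ordinal);
- that the three AUCs and the Model 3 minus Model 1 difference are reported after bootstrap optimism correction, refitting the models in each of at least 500 resamples, with bootstrap 95% CIs;
- that the conclusion on the primary aim rests on these results.

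If a fuller plan already contains this, a sentence pointing to it is enough. No new data are needed, and the article reports that the database is not yet closed. The cost is a little more analysis work and slightly lower reported AUCs. If cases turn out to be very few, the likelihood-ratio test may run slightly above its nominal level, as the 4.4% prevalence runs show.
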